**Fig 3 pone.0284381.g003:**
[figure not shown]
The location of the region of interest. The blue dots are centered on the acupoint positioning.

### Privacy protection

Since participants will be required to take off their lower body clothes during IRT image collection, their privacy needs to be protected as follows:

The image collecting site will be separated from the outside environment by a movable screen.When removing the lower clothes, participants will keep their underwear to maximize their privacy.

### Other measurements

#### Demographic data

Demographic data included gender, age, ethnicity, education, height, weight, BMI, etc. These data will be collected from all participants.

#### Disease-related data

Disease-related data included NRS [29], pain sites (front, back, outside or inside), duration of pain, pain descriptors (stabbing, bursting, sore, burning, etc.), pain activities (going upstairs, going downstairs, standing up, walking, etc.).

The primary outcomes included the relative skin temperature of 11 acupoints, and the secondary outcomes included the absolute skin temperature of 11 acupoints and other measurements.

### Sample size calculation

The relative skin temperatures of 11 acupoints are the primary outcomes of this study. The relative skin temperature of acupoints were preliminary extracted from the IRT images of 30 KOA patients and 30 healthy individuals at the clinic. The mean values of the KOA and healthy groups were 0.11°C and -0.23°C respectively, with the same standard deviation of 0.79°C in both groups. With 2-sided α = 0.0045 (adjusted for 11 primary outcomes using Bonferroni adjustment), 149 participants will be needed to provide 80% statistical power. Considering an attrition rate of 15%, a total of 340 participants (170 per group) are expected to be recruited.

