To our knowledge, this is the first study to investigate the skin temperature of acupoints in KOA patients. IRT technology has the characteristics of noninvasive, nonradiation, noncontact and high repeatability. It is currently one of the best methods to measure the skin temperature of acupoints. For inflammatory diseases such as KOA, IRT can simply and clearly reflect the condition and guide medical treatment [15]. This will be a multicenter study in which patients will be recruited from primary and tertiary hospitals simultaneously. Patients included in this study will be a typical KOA population with any KL grade other than grade I, which is undiagnosable. Patients who underwent knee surgery or report NRS scores less than 4 will be excluded because we cannot ensure the stability of the lower extremity temperature in this population. Acupoints assessed will be the most common ones in clinical practice. Moreover, two temperature correction methods, an adequate sample size and a strictly corrected P value increase the credibility of this study.

This study still has a few limitations. First, the location of the ROI drawn by different researchers may be slightly different since the positioning of acupoints are rough positions rather than precise points. However, ROIs will be drawn repeatedly by different researchers to ensure the consistency of acupoint location. Second, this study only focused on skin temperature at acupoints, which is of limited reference value to therapies other than acupuncture.

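### Minor attrition-inflation error: 149 per group with 15% loss requires 176 per group, not 170, so power at the stated loss is about 78% to 79% rather than 80%

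*Protocol article*

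**What the plan says.** The Sample size calculation section of the protocol article takes its inputs from preliminary images of 30 patients and 30 healthy individuals: "The mean values of the KOA and healthy groups were 0.11°C and -0.23°C respectively", "with the same standard deviation of 0.79°C in both groups". The significance level is given as "With 2-sided α = 0.0045 (adjusted for 11 primary outcomes using Bonferroni adjustment". The result is that "149 participants will be needed to provide 80% statistical power", with no statement of whether this is per group or in total. The next sentence gives the recruitment target: "Considering an attrition rate of 15%, a total of 340 participants (170 per group) are expected to be recruited". The Abstract and the Study design section repeat 340 in total and 170 per group. The Discussion lists the sample size among the study's strengths: "an adequate sample size and a strictly corrected P value increase the credibility of this study".

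**The concern.** Attrition is removed from the number recruited, so the number required must be divided by the retained fraction. Taking 15% from 170 leaves 144.5, which is below 149. The three stated figures (149 needed, 15% lost, 170 recruited) therefore cannot all hold. What is at stake is the power claim: at the attrition rate the protocol chose for itself, the analysable number and the 80% power are both missed. A smaller point adds to this. Because 149 carries no unit, a reader has to redo the calculation to confirm what it counts.

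**Working it through.** **Inputs, all from the Sample size calculation section.** Means 0.11 and -0.23°C, so the difference is 0.11 - (-0.23) = 0.34°C; SD 0.79°C in both groups; two-sided alpha 0.0045 (0.05/11 = 0.004545, rounded); power 80%; attrition 15%; planned recruitment 170 per group, hence 1:1.

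**Step 1: reproduce 149.** The normal approximation is

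n per group = 2 × (SD/difference)² × (z for alpha/2 + z for power)² = 2 × (0.79/0.34)² × (2.841 + 0.842)² ≈ 146.4 (with unrounded quantiles), so 147.

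The exact two-sample t-test uses the noncentral t distribution with 2n - 2 degrees of freedom and noncentrality (0.34/0.79) × √(n/2). It gives 79.8% power at n = 148 and 80.2% at n = 149. So 149 is the smallest per-group number that reaches 80%. It matches the protocol's figure exactly and has no margin to spare. Using 0.05/11 in place of 0.0045 also gives 149.

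**Step 2: inflate for 15% attrition.**
- Correct rule: 149/(1 - 0.15) = 175.3, so 176 per group, 352 in total. That is 6 more per group and 12 more in total than planned.
- Common shortcut: 149 × 1.15 = 171.35, so 172 if rounded up. This is close to 170 but does not give it.
- Starting from the normal-approximation figure: 147/0.85 = 172.9, so 173 per group, still above 170.

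**Step 3: what 170 per group delivers.** 170 × 0.85 = 144.5, so 144 or 145 per group analysed.

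| Analysed per group | Loss from 170 | Power, t-test | Power, normal approximation |
|---|---|---|---|
| 170 | none | 86.5% | 87.0% |
| 149 | 21/170 = 12.4% | 80.2% | 80.9% |
| 145 | 25/170 = 14.7% | 78.8% | 79.5% |
| 144 | 26/170 = 15.3% | 78.4% | 79.1% |

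At 144 per group the shortfall against 80% is 80 - 78.4 = 1.6 points (t-test) or 80 - 79.1 = 0.9 points (normal approximation). The largest loss that still leaves 149 per group is 1 - 149/170 = 12.4%.

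**The case against.** Several points on the other side are sound and limit the finding.

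- **The loss of power is slight.** It is 0.9 to 1.6 points. The Statistical analysis section names a Z test for the group comparisons, and on that basis the need is 147 per group and the gap is smaller still. This stands.
- **It arises only near the full 15%.** Participants complete questionnaires and an infrared examination after consent, and no follow-up visit is described. The 15% is best seen as an allowance for unusable records, and actual loss may well be lower. This stands as a condition on the result, but 15% is the rate the protocol uses to justify 340, so the sentence should be right at that rate. The planned mean/mode imputation does not rescue it: it keeps the head count but does not restore lost information.
- **The inputs are far less certain than the error.** With 30 per group, the standard error of the preliminary difference is about 0.79 × √(2/30) = 0.20°C, against a difference of 0.34°C. One difference and one SD also stand for 11 acupoints. A gap of about 5 per group is small beside that. This bears on how much the error matters, not on whether the figures agree.
- **170 may be the shortcut, rounded.** It lies within 1% of 171.35. That may explain where 170 came from, but the shortcut under-inflates, so it does not make the figure correct.

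A reader might go further in two ways. The first is to take 149 as a study total and conclude that the study is badly underpowered. The text rules this out: the next sentence gives 170 per group, and inflating a total of 149 by 15% would give about 176 in all (149/0.85 = 175.3), nowhere near 340. The second is to infer that the sample size is materially inadequate and that the Discussion's claim is false. Power running from about 78% at 15% loss to about 87% with none does not support that.

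**Conclusion.** The point holds as a minor inflation error. On the protocol's own difference, SD, alpha and power, 149 is a per-group number, and with 15% attrition it requires 176 per group rather than 170. If the whole 15% is lost, power is about 78% to 79% instead of the stated 80%; the target is met for loss up to about 12%. These figures assume equal groups, equal loss in both, a comparison of two means for a single acupoint at 0.0045, and that the preliminary difference and SD apply to that acupoint. No test, threshold or conclusion in the plan changes.

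**What to change.** In the Sample size calculation section, write that 149 participants *per group* are needed. Then replace the attrition claim with what 170 per group supports: at least 80% power if no more than about 12% of each group is lost, about 78% at 15% loss, and about 87% with no loss. This costs one sentence and a slightly less favourable power statement, with no extra recruitment. The Discussion's remark on sample size can stay.

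If the sponsor prefers to keep both 15% attrition and 80% power as stated, the target becomes 176 per group (352 in total). That means 12 more participants and matching changes wherever 340 and 170 appear, including the Abstract and the Study design section. The small gain in power does not make this necessary.

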### Data correction and statistical analysis

#### Correction of skin temperature

Human skin temperature is individual and affected by basal body temperature [30]. A previous study [31] showed that relative temperature, which can control bias from individual differences, is more valuable than absolute temperature under specific conditions. Relative temperature can eliminate the systematic error caused by factors such as body and ambient temperature, and truly express the temperature characteristics in the ROI. Using the quantification method of relative temperature, the temperature value in the ROI will be subtracted from the temperature value of other regions (reference areas) specified in the same image. In this study, at the same time that the absolute temperature will be reported, relative temperature will be analyzed as the main indicator. The specific correction formula for relative temperature is as follows:

$$T_{c}=T-\bar{T}$$

*T_c_* is the measured value of the skin temperature of the acupoint after correction. *T* is the absolute skin temperature of the acupoint (the actual value measured). $\bar{T}$ is the control temperature, means the average skin temperature of the corresponding reference area. As shown in Fig 4, the reference area is the entire lower limb region on the IRT image which used to locate the acupoint.

**Fig 4 pone.0284381.g004:**
[figure not shown]
The location of reference areas.

#### Statistical analysis

For this study, the statistical analysts will be blinded. SAS version 9.3 (SAS Institute, Cary, NC, USA) or R software will be used for statistical analysis. Measurement data will be described as the mean ± standard deviation (M±SD) or median and interquartile ranges, and counting data will be described as frequency, constituent ratio or percentage. Independent samples t-tests or χ2 tests will be used to test the equilibrium of demographic data with a significance level of 0.05. The intraclass correlation coefficient (ICC) will be used to obtain the test-retest reliability of the temperature extracted by different researchers. A two-way random model with absolute agreement will be used for ICC calculation. An ICC value greater than 0.75 for each relative skin temperature of the acupoints evaluated will be considered to have good reliability. Comparison of relative skin temperature and absolute skin temperature between groups will be performed by Z test or χ2 test. For the relative skin temperature of acupoints, P < 0.0045 will be considered statistically significant. For other measurements, P < 0.05 will be considered statistically significant. Missing values and extreme values in demographic data will be confirmed and modified by phone calls before analysis. Other missing data will be inputted by the mean/mode completer.

Exploratory analysis will include the exploration of correlations and contributory factors within relative skin temperature at different acupoints. To simplify the factor structure of multiple relative skin temperatures of acupoints, when Kaiser-Meyer-Olkin (KMO) measurement value is > = 0.5 and Bartlett’s sphericity test value is <0.05, exploratory factor analysis will be adopted. After clustering and dimensionality reduction of temperature in two groups, the common factors will be extracted by principal component analysis. Then, the Kaiser normalized maximum variance method will be used to calculate the factor loading and factor score coefficient matrix to obtain the score of each common factors and acupoints’ relative skin temperature. A general linear regression model will be used to explore the influence some factors on skin temperature of acupoints. In the model, dependent variable will be the comprehensive factor scores; fixed factors will include age, gender, BMI, pain site and NRS, among which age and BMI will be transformed into qualitative data.

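### The fixed 0.0045 cut-off for the 11 primary acupoint comparisons is valid but gives away power that Holm's procedure would recover under the same familywise error; the role of the 11 absolute-temperature tests should also be stated

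*Protocol article*

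**What the plan says.** The Sample size calculation section states: "The relative skin temperatures of 11 acupoints are the primary outcomes of this study". It sets a two-sided alpha of 0.0045, "adjusted for 11 primary outcomes using Bonferroni adjustment". The Statistical analysis section carries the same figure into the analysis as one cut-off for every acupoint: "For the relative skin temperature of acupoints, P < 0.0045 will be considered statistically significant". No step-down or other sequential rule is described.

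The same section also plans between-group tests on both scales: "Comparison of relative skin temperature and absolute skin temperature between groups will be performed by Z test or χ2 test". It then adds: "For other measurements, P < 0.05 will be considered statistically significant". Under Disease-related data, "the secondary outcomes included the absolute skin temperature of 11 acupoints and other measurements". The section on correction of skin temperature makes relative temperature the main indicator and says that absolute temperature will be reported alongside it.

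The Discussion expects differences at some of the 11 acupoints and does not say how many. It describes the result as evidence on which acupoints are abnormal, with a randomised trial of temperature-guided selection to follow.

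**The concern.** The product of the study is a list of acupoints, so a true difference that is missed matters as much as one that is wrongly included. A fixed cut-off holds each acupoint to 0.0045 however many others have already been rejected. Once some hypotheses are rejected, fewer remain that could be rejected falsely, and the threshold can be relaxed without exceeding 5% familywise error. Holm does this and single-step Bonferroni does not. The loss grows with the number of acupoints that truly differ.

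The absolute temperatures raise a lesser matter. They are the same 11 sites before the reference mean is subtracted. If they are tested at 0.05 with no stated role, a reader could take an acupoint that fails on the primary scale and call it abnormal on the other.

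**Working it through.** **Inputs from the article (Sample size calculation).** "The mean values of the KOA and healthy groups were 0.11°C and -0.23°C respectively", a difference of 0.11 − (−0.23) = 0.34 °C. SD 0.79 °C in both groups; two-sided alpha 0.0045; 80% power; 149 participants, which is per group; 170 per group recruited, with 15% attrition.

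**Assumptions not in the article.** The difference is 0.34 °C at every truly differing acupoint and zero elsewhere. The 11 test statistics are equally correlated. The number of differing acupoints is varied.

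**1. The plan's own figures.** 0.05/11 = 0.004545, stated as 0.0045. At that alpha the normal approximation gives 147 per group. The two-sample t-test (noncentral t) gives 149 per group with power 80.2%. The stated 149 is reproduced. Familywise error is at most 11 × 0.0045 = 0.0495.

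**2. Holm's thresholds.** Order the p-values and compare the j-th smallest with 0.05/(11 − j + 1): 0.00455, 0.00500, 0.00556, 0.00625, 0.00714, 0.00833, 0.0100, 0.0125, 0.0167, 0.025, 0.05, stopping at the first failure. None of these is below 0.0045, so every Bonferroni rejection is also a Holm rejection.

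**3. Power at 149 per group.** Standard error = 0.79 × √(2/149) = 0.0915, so the noncentrality is 0.34/0.0915 = 3.71. Simulation of 11 z statistics, 200,000 runs, gives this average power per truly differing acupoint:

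| Acupoints that differ | Bonferroni | Holm, correlation 0.3 | Holm, correlation 0.5 |
|---|---|---|---|
| 1 | 81% | 81.0% | 81.0% |
| 3 | 81% | 82.1% | 82.2% |
| 6 | 81% | 84.6% | 84.3% |
| 9 | 81% | 88.0% | 87.4% |
| 11 | 81% | 91.6% | 90.5% |

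Bonferroni is 80.9% here, against 80.2% in step 1, because z statistics are used in place of t. The chance of finding every differing acupoint moves more. At correlation 0.5 it rises from 49% to 59% with six differing and from 38% to 75% with all 11. Across assumed correlations of 0 to 0.9, Holm's simulated familywise error was never above 0.048.

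**4. After attrition.** 170 × 0.85 = 144.5, so about 144 per group remain. Bonferroni power there is 79%. Holm at 144 gives 79.3% with one differing acupoint, about 80.5% with three and 81.2% with four.

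**5. Absolute temperatures, 11 tests at 0.05 with no true difference.** If independent, 1 − 0.95^11 = 0.431. Simulated: 30% at correlation 0.5, 18% at 0.8 and 13% at 0.9. The expected number of false positives is 11 × 0.05 = 0.55 at any correlation.

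**The case against.** The best defence is that nothing here is wrong. Bonferroni is prespecified, the sample size is built on it, the analysis applies the same threshold, and each acupoint has its planned 80% power before attrition. All of that stands. It does not make the choice neutral, because Holm needs no further data, assumptions or participants and cannot reject less. It is also fair that the gain is small if few acupoints differ: about 0.1 percentage point with one and 1.3 with three. The larger gains need most sites to differ by the full 0.34 °C, and the article does not say which acupoint or acupoints its pair of pilot means describes.

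Two stronger readings are tempting and not supported. One is that Holm more than pays back the power lost because 170 per group leaves about 144. Step 4 shows that it regains the 81% of Bonferroni at 149 only if about four or more acupoints differ. The other is that the plan opens a formal second route by which absolute temperature can declare an acupoint abnormal at 0.05. These outcomes are labelled secondary, relative temperature is the main indicator, and no sentence lets absolute temperature alone decide. The 0.05 rule does not name them either. It refers to other measurements, a phrase that the outcome list sets beside absolute temperature, not over it. Reading the rule as covering them is natural but not explicit, and on either reading no multiplicity control is stated. Whether to adjust secondary tests is a trade-off, and many plans do not.

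**Conclusion.** The primary rule is valid but inefficient. Under the assumptions above, Holm adds between almost nothing (one differing acupoint) and about 10 percentage points (all 11) to the average power per differing acupoint, within the same 5% familywise limit. The Discussion's expectation of differences at some acupoints makes a gain likely, but its size cannot be fixed from the article. This is a worthwhile refinement and not a defect that threatens the primary conclusions.

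For the absolute temperatures, the finding is only that their role is not spelled out. The familywise error under a global null is about 13-30% for correlations of 0.9 to 0.5. The 43% figure needs independence, which is implausible for sites on one limb that share body and ambient temperature.

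**What to change.** Replace the fixed cut-off in the Statistical analysis section with Holm-adjusted p-values at familywise 0.05 across the 11 relative temperatures. Keep 0.0045 for the sample size and for simultaneous confidence intervals. Add one sentence saying that the 11 absolute-temperature comparisons are supportive and cannot by themselves mark an acupoint as abnormal.

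The cost is wording, settled before the analysts are unblinded. One small drawback should be acknowledged in the text: an acupoint can be significant by Holm while its Bonferroni interval still includes zero.

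### Missing primary temperatures are to be filled with an unspecified mean and tested at 0.0045, which either understates the standard error or shrinks the estimated difference, in proportion to the share missing

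*Protocol article*

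**What the plan says.** The Statistical analysis section has two missing-data rules. The first covers demographic data: "Missing values and extreme values in demographic data will be confirmed and modified by phone calls before analysis". The second covers the rest: "Other missing data will be inputted by the mean/mode completer". Once demographic data are set aside, what remains is the skin temperatures and the disease-related data, including the numerical rating scale (NRS) for pain. Nothing exempts the primary outcomes, which the Sample size calculation section identifies: "The relative skin temperatures of 11 acupoints are the primary outcomes of this study".

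The threshold for those outcomes is fixed in the same paragraph as the filling rule: "For the relative skin temperature of acupoints, P < 0.0045 will be considered statistically significant". No adjustment of the standard error for filled values is described, and the article does not say whose mean is meant.

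The only figure for loss is in the Sample size calculation section: "Considering an attrition rate of 15%, a total of 340 participants (170 per group) are expected to be recruited".

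**The concern.** A filled mean is not an observation. If each group is filled with its own mean, the filled values add nothing to the sum of squares but still count in the sample size, so the standard error is too small and the test rejects too often. If both groups are filled with the overall mean, cases and controls receive the same value and the estimated difference is pulled toward zero.

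The Discussion offers the strict correction of the P value as a strength of the study. It also says the results will show which acupoints are abnormal in patients and will lead to a randomised trial of temperature-guided acupoint selection. False positives or attenuated differences would carry into that work. Leaving the choice of mean open adds a further problem: if it is made after the data are seen, it can affect which acupoints are declared different.

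**Working it through.** **Inputs, all from the Sample size calculation section.** "The mean values of the KOA and healthy groups were 0.11°C and -0.23°C respectively", so the difference is 0.11 − (−0.23) = 0.34 °C. The SD is 0.79 °C in both groups. "With 2-sided α = 0.0045 (adjusted for 11 primary outcomes using Bonferroni adjustment" agrees with 0.05/11 = 0.00455. Recruitment is n = 170 per group.

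**Step 1: the plan's own figure.** The article says "149 participants will be needed to provide 80% statistical power". The normal formula gives 2 × (2.841 + 0.842)² × 0.79² / 0.34² ≈ 146.5, so 147 per group. The noncentral-t calculation gives exactly 149 per group. The stated figure is reproduced, read as per group.

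**Step 2: group-mean filling.** Let a share f be missing completely at random in each group, leaving m = n(1 − f) observed.

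- The true SE of the difference is SD × √(2/m).
- After filling, the variance estimate is multiplied by (m − 1)/(n − 1) and the SE is computed with n in place of m.
- The ratio of estimated to true SE is therefore √[m(m − 1) / (n(n − 1))], close to 1 − f.
- The actual type I error is 2 × [1 − Φ(2.841 × ratio)].

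At f = 15%, m = 144.5. The ratio is √(144.5 × 143.5 / (170 × 169)) = 0.850, and the error is 2 × [1 − Φ(2.414)] = 0.0158.

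**Step 3: overall-mean filling.** Each group mean becomes (1 − f) × observed mean + f × common value, so the expected difference is 0.34 × (1 − f).

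| Missing share | Group mean: type I error per acupoint | Multiple of 0.0045 | Overall mean: expected difference (°C) |
|---|---|---|---|
| 1% | 0.0049 | 1.1 | 0.337 |
| 2% | 0.0054 | 1.2 | 0.333 |
| 5% | 0.0070 | 1.5 | 0.323 |
| 10% | 0.0106 | 2.4 | 0.306 |
| 12.4% (149 of 170 observed) | 0.0128 | 2.8 | 0.298 |
| 15% | 0.0158 | 3.5 | 0.289 |

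**Step 4: check by simulation** (4 million runs under no difference, 400,000 under 0.34 °C, 170 per group).

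- At 15% missing in both groups, the type I error is 0.0161 with group-mean filling, 0.0045 with overall-mean filling and 0.0045 with observed data only.
- Power is 78.3% both for overall-mean filling and for observed data only. Overall-mean filling shrinks the SE along with the difference, so the test itself is almost unchanged.
- With unequal loss of 25%/5% and 30%/0%, overall-mean filling gives 0.0042 and 0.0039, slightly conservative. Group-mean filling gives 0.0162 and 0.0174.

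**Step 5: across the 11 acupoints.** With group-mean filling at 15%, the Bonferroni bound rises from 0.05 to 11 × 0.0158 ≈ 0.17. If the acupoints were independent, the chance of at least one false positive would be 1 − (1 − 0.0158)¹¹ ≈ 0.16. At 5% missing the independent figure is about 0.074.

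**The case against.** A reader might infer that the rule makes the primary tests invalid whichever mean is used. The documents do not support that. They do not say that filling is within group, and under overall-mean filling the test keeps its level and has the same power as an analysis of observed data. Only the estimate is biased. Blinding of the analysts does not settle which mean is meant, because coded groups still allow group means.

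A reader might also take 15% as the plan's expected share of filled temperatures. The article gives it only as an allowance for attrition when setting recruitment. Recruiting extra participants makes most sense if those lost leave the analysis. This is a cross-sectional study with one thermography examination, so a person lost before imaging may never enter the analysis set. The stored file holds temperatures across the whole field of view, so an acupoint in view can be extracted again, and Quality control provides for regular completeness checks. The missing share among analysed participants may well be small, and at 1% to 5% the inflation is 1.1 to 1.5 times.

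The familywise figure of 0.16 assumes independent acupoints. These points lie on one limb, many around one knee, and the plan itself provides for factor analysis of them; positive correlation would lower that figure.

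These objections stand and limit the size of the problem. They do not rescue the rule: at any missing share above zero it either understates the SE or attenuates the difference, and it offers no gain over analysing what was observed.

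**Conclusion.** The point holds in limited form. The article fixes a filling rule that covers the primary outcomes, leaves the kind of mean open, and applies the 0.0045 threshold to the filled data uncorrected.

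The harm depends on the reading. Group-mean filling raises the per-acupoint type I error, modestly at low missingness and to about 0.016 at most over the range examined with equal loss. Overall-mean filling leaves the error rate intact and understates the difference by the missing share. Because the plan does not choose, it does not secure the error control it claims, but neither is that control shown to be lost.

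The main figures assume values missing completely at random, equal loss in the two groups and 170 per group. The 15% row further assumes that everyone covered by the attrition allowance stays in the analysis and has temperatures filled, which the article does not state. The effect of filling missing NRS scores was not quantified.

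**What to change.** Delete mean/mode filling for the skin temperatures and the NRS. State that the primary comparison at each acupoint uses observed relative temperatures. If missingness is not negligible, add multiple imputation combined by Rubin's rules as a sensitivity analysis, with group in the imputation model. Make the change before the data are analysed.

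Under random loss this restores 0.0045 per acupoint and an unbiased 0.34 °C. Power is 80% with 149 observed per group. If 15% are truly lost, 144 to 145 remain per group and power is about 78–79%, because 170 covers a loss of only 1 − 149/170 = 12.4% (149/0.85 = 175.3, so 176 per group would be needed). Relative to overall-mean filling, no power is given up. Relative to group-mean filling, what is given up is a rejection rate inflated by the understated SE.

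Otherwise the cost is a sentence of wording and light programming. Covariate adjustment of the primary comparison is a separate question and is not needed for this fix.
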